# Study Assessments and Procedures

This section lists the parameters of each planned study assessment. The exact timing of each assessment is listed in the Time and Events Table (Section 4.4). Detailed procedures for obtaining each assessment are provided in the Study Procedures Manual (SPM). Whenever vital signs and blood draws are scheduled for the same nominal time, the assessments should occur in the following order: vital signs, blood draws. The timing of the assessments should allow the blood draw to occur at the exact nominal time.

The timing and number of planned study assessments, including safety, pharmacokinetic, pharmacodynamic/biomarker or others assessments may be altered during the course of the study based on newly available data to ensure appropriate monitoring. The change in timing or addition of time points for any planned study assessments must be approved and documented by GSK, but this will not constitute a protocol amendment. The IEC will be informed of any safety issues that require alteration of the safety monitoring scheme. No more than 500 mL of blood will be collected over the duration of the study, including any extra assessments that may be required.

## Screening

Volunteers will be invited to attend a consent talk at the Clinical Unit Cambridge (CUC) and, if they decide to participate in the study, they will be screened to check whether they are eligible for the study. Screening will take place up to 30 days inclusive before a volunteer is admitted to the unit for the start of the study treatment period. The screening visit will take approximately 4 hours, during which subjects will be consented and undergo a medical examination - which will include a medical history, assessment of vital signs (blood pressure and pulse rate), ECG, a urine drug screen for drugs of abuse and alcohol breath test.

### Demographic/Medical History Assessments

The following demographic parameters will be captured: date of birth, gender, race and ethnicity.

Medical/medication/alcohol history will be assessed as related to the eligibility criteria listed in Section 5.2.

### Safety

Planned time points for all safety assessments are listed in the Time and Events Table (Section4 5). Additional time points for safety tests such as vital signs, physical exams and laboratory safety tests may be added during the course of the study based on newly available data to ensure appropriate safety monitoring.

Physical Exams

- A complete physical examination will include assessments of the head, eyes, ears, nose, throat, skin, thyroid, neurological, lungs, cardiovascular, abdomen (liver and spleen), lymph nodes and extremities. Weight will also be measured and recorded.

Vital Signs

- Vital sign measurements will include systolic and diastolic blood pressure and pulse rate.

Clinical Laboratory Assessments

Hematology, clinical chemistry, urinalysis and additional parameters to be tested are listed below:

| **Hematology** | | |
| --- | --- | --- |
| Platelet Count | *RBC Indices*: | *Automated WBC Differential:* |
| RBC Count | MCV | Neutrophils |
| WBC Count (absolute) | MCH | Lymphocytes |
| Hemoglobin | MCHC | Monocytes |
| Hematocrit |  | Eosinophils |
|  |  | Basophils |

| **Clinical Chemistry** | | | |
| --- | --- | --- | --- |
| BUN | Potassium | AST (SGOT) | Total and direct bilirubin |
| Creatinine clearance | Chloride | ALT (SGPT) | Albumin |
| Glucose | Total CO_2_ | GGT | Total Protein |
| Sodium | Calcium | Alkaline phosphatase | apolipoproteins |
| HDL cholesterol | LDL cholesterol | Fasting triglycerides | Total Cholesterol |
| 24hr triglyceride profile |  |  |  |

| **Other screening tests** |
| --- |
| HbA1c |
| Fasting lipid profile |
| FSH and oestradiol (as needed in women of non-child bearing potential only) |
| Alcohol breath, urine drug screen (to include at minimum: amphetamines, barbiturates, cocaine, opiates, cannabinoids and benzodiazepines). |

## Study visit

### Faecal Collection

One or all faecal samples passed during each study visit will be collected, weighed and stored prior to shipment to GSK for analysis for faecal bile acid profiles. In the event that subjects do not pass any faeces while in the unit, the first stool sample passed after discharge will be collected at home and shipped back to CUC-GSK.

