# OBJECTIVE(S)

## Primary

To investigate the relationship between the glucose lowering action of metformin and:

- Faecal and serum bile acid concentrations
- Enteroendocrine peptide profiles including but not limited to incretins and PYY
- Lipid metabolism including but not limited to fasting lipids and prandial TGs

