# ENDPOINT(S)

## Primary

During metformin wash out and when treatment reinstated, pharmacodynamic endpoints will include the following as data permit:

- 24h profiles of blood glucose and insulin
- Faecal and serum bile acid profiles
- Enteroendocrine peptide profiling including but not limited to tGLP-1, tGIP, and tPYY
- Serum lipid analysis including but not limited to fasting HDL and LDL cholesterol, fasting and prandial TGs, ApoA1, ApoB and ApoE

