### Study Visits

Visit 1

Within approximately 30 days of screening, eligible subjects who provide informed consent will attend the unit for the first study visit lasting approximately 30 hrs. This visit serves as a baseline session during which the following will occur, (see time and events Section 4.4 and Section 7 for details);

- Routine admission assessments
- Blood glucose diary review
- Pharmacodynamic blood sampling for entero-endocrine peptide profiling, serum bile acid and lipid profile
- Faecal collection (bile acids)
- Enterotest duodenal bile collection (bile acids)

Subjects will be admitted to the unit on the late afternoon / evening before PD profiling is due to start. They will be given a standard meal at approximately 6pm and then fasted, except water, from 10pm onwards. At approximately 12am, patients will be asked to swallow the EnteroTest, and the string will remain in situ overnight. The following morning PD blood sampling will begin, followed by the administration of a food cue to trigger gall bladder contraction, the resulting bile being collected by the string, which will be removed 1 hour later. Following initial assessments and testing, metformin will be dosed with a breakfast served at approximately 8am. Further assessments will be timed from the beginning of this meal and are detailed in Section 4.4. The assessments and procedures carried out in each of the 4 study visits will be the same.

Visit 2

Following discharge from the unit post Visit 1, patients will refrain from taking metformin. They will closely monitor their CBG each morning fasting before breakfast and before dinner, continuing to record it in a diary card. Approximately 7 days later they will return for study visit 2. Pharmacodynamic samples, faecal and bile acid collections will be repeated according to the schedule detailed in Section 4.4.

Visit 3

On discharge patients will continue to abstain from metformin and once their mean CBG increases by approximately 25%, from baseline (based on the 7 day average of fasting CBG before Visit 1) or approximately three weeks from the beginning of wash-out, they will be informed by the study co-ordinator to attend for Visit 3. Pharmacodynamic samples, faecal and bile acid collections will be repeated according to the schedule detailed in Section 4.4.

Visit 4

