Upon discharge from Visit 3, subjects will resume their usual prescribed dose of metformin treatment and return to the unit for study Visit 4 once their fasting CBG returns to their baseline level (approximate) or achieve clinically acceptable gycaemic control, as determined by the principal investigator. Pharmacodynamic samples, faecal and bile acid collections will be repeated according to the schedule detailed in Section 4.4.

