4.4 Time and Events Table (continued)

| 1. Sample collection times are approximate and may vary as testing dictates 2. A single or all faecal samples passed may be taken over the duration of each study visit. If the patients do not have any bowel movement during their visit, their first faecal sample passed after discharge will be collected at home and shipped back to the GSK Clinical Unit. 3. Time of discharge may vary and will not be before all assessments have been completed 4. PD blood samples scheduled to be taken at the same time as a meal will be taken pre meal |
| --- |

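### The fallback stool is passed after metformin has been stopped or resumed, so the primary Visit 1 to Visit 3 faecal bile acid contrast is not assured to compare on-drug with off-drug samples

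*Protocol*

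**What the plan says.** **Role of the measure.** The primary objective relates glucose lowering to "Faecal and serum bile acid concentrations", and the primary endpoints list "Faecal and serum bile acid profiles". The estimation aim under Hypotheses and Treatment Comparisons also speaks of concentrations. The Pharmacodynamic/Biomarker Analyses section puts the Visit 1 to Visit 3 difference first, because the largest changes are expected there.

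**Collection.** The Faecal Collection section says "One or all faecal samples passed during each study visit will be collected, weighed and stored". Footnote 2 of the Time and Events Table (section 4.4) says "A single or all faecal samples passed may be taken over the duration of each study visit". Neither says how to choose, or whether the choice must be the same at each visit. If nothing is passed in the unit, "the first stool sample passed after discharge will be collected at home and shipped back to CUC-GSK"; footnote 2 gives the same fallback. No time limit is set. The protocol asks for the actual date and time of each pharmacokinetic blood sample, but states no such requirement for stools.

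**Drug state around discharge (Study Visits).**
- After Visit 1: "Following discharge from the unit post Visit 1, patients will refrain from taking metformin".
- After Visit 2: "On discharge patients will continue to abstain from metformin".
- After Visit 3: "Upon discharge from Visit 3, subjects will resume their usual prescribed dose of metformin treatment".

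The Discussion of Design adds an exception. If fasting glucose rises by the required amount within 7 days of Visit 1, Visit 3 is dropped and metformin restarts once Visit 2 is complete.

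**The concern.** The fallback is harmless where discharge leaves the drug state unchanged. It is not clearly harmless at the two visits that form the main contrast. A Visit 1 fallback stool is meant to represent the on-drug state but is passed after metformin has been stopped. A Visit 3 fallback stool is meant to represent the off-drug state but is passed once metformin is due to be resumed.

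To the extent that such a stool already reflects the new state, Visit 1 moves towards off-drug and Visit 3 towards on-drug. The two errors add up and do not cancel. With about 12 evaluable subjects, each fallback user is 1/12, or about 8%, of the sample at that visit. The primary aim is a relationship with glucose, so a distortion that differs between subjects by bowel habit would also tend to blur the correlations of change.

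**Working it through.** **1. The plan's own figure.** The protocol gives no standard deviation, effect size or precision for the faecal measure. Its only general precision figure is a 95% CI half-width of 0.62 SD_b for a mean with n = 12. It reproduces as t(0.975, 11) × c4(12) / √12 = 2.201 × 0.9776 / 3.464 = 0.621, where c4 is the expected sample SD divided by the true SD. That figure is not in dispute, and it says nothing about bias from the sampling rule.

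**2. Where the fallback crosses a switch.**

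| Visit | State during stay | State after discharge | Fallback crosses a switch? |
|---|---|---|---|
| 1 | on | off | yes |
| 2 | off | off (on if Visit 3 is dropped) | only if Visit 3 is dropped |
| 3 | off | on | yes |
| 4 | on | on | no |

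**3. Effect on the contrast.** Let D be the true mean on-minus-off difference on the analysis scale. Let f be the share of subjects using the fallback at a visit, and w the share of that stool's signal that reflects the new state.
- Observed Visit 1 mean = on − f1·w1·D
- Observed Visit 3 mean = off + f3·w3·D
- Observed / true difference = 1 − f1·w1 − f3·w3

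Neither f nor w is in the documents. With assumed values, equal at both visits (ratio = 1 − 2·f·w):

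| f | w = 0 | w = 0.25 | w = 0.5 | w = 1 |
|---|---|---|---|---|
| 0.10 | 1.00 | 0.95 | 0.90 | 0.80 |
| 0.25 | 1.00 | 0.875 | 0.75 | 0.50 |
| 0.50 | 1.00 | 0.75 | 0.50 | 0.00 |

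For f = 0.25 (3 of 12 subjects) the loss is 2 × 0.25 × 0.25 = 12.5% up to 2 × 0.25 × 0.5 = 25%. If the fallback is needed at only one of the two visits, the loss is half of that: 6.25% to 12.5%. For a subject whose Visit 3 is dropped, the same formula applies with Visit 2 in place of Visit 3, if Visit 2 serves as that subject's off-drug value.

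**4. One stool or all stools.** Let s be the share of the variance of a single-stool value that is stool-to-stool variation (assumed), with k1 and k3 stools averaged at Visits 1 and 3. Relative to one stool at each visit, the SD of the change is √{[2(1 − s) + s/k1 + s/k3] / 2}. With s = 0.5:
- one and three stools: √[(1 + 0.5 + 0.167) / 2] = 0.91
- three and three stools: √[(1 + 0.167 + 0.167) / 2] = 0.82

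For a concentration, a varying stool count therefore changes the precision, provided that stools within a visit share the same expected concentration.

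**The case against.** Four objections deserve weight.

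**The stool may still reflect the earlier state.** The fallback arises only after a stay of about 30 hours without a bowel movement, and at Visit 1 metformin is given with breakfast during that stay. The next stool may largely represent the on-drug period. At Visit 3 it may even be passed before the first resumed dose. The design itself expects slow change: it cites complex gut kinetics and allows up to about three weeks of washout before Visit 3. This stands, and w could be near zero. But with no time limit and no stated recording of passage time, nobody could show that it was.

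**The size is assumed.** This stands too. The study is sized on feasibility and tests no hypothesis, and no figure in the protocol fixes f or w.

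**Detail belongs in the Study Procedures Manual or the SAP.** The protocol does send detailed procedures, including the quantity of biomarker samples, to the manual, and neither document is shown. Stool selection and time recording may be settled there. The post-discharge fallback, however, is fixed in the protocol itself, in two places. An analysis plan cannot recover a passage time that was not recorded.

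**A stronger reading of the stool-count rule.** A reader might infer that taking one stool at one visit and two at another would double the faecal result with no drug effect. That would require total bile acid content as the endpoint. The objective and the estimation aim name concentrations, and weighing the stool does not turn the endpoint into a total. The documents do not support that reading.

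**Conclusion.** The point holds in a limited form. For subjects who supply a fallback stool at Visit 1 or Visit 3, or at Visit 2 when Visit 3 is dropped, the faecal bile acid contrast is not assured to compare on-drug with off-drug samples. Any resulting bias runs towards no difference. It ranges from nothing (w = 0) to a loss of 12.5% to 25% under the assumed f = 25% and w = 25% to 50% at both visits; other assumptions give other values.

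It would go too far to conclude that the faecal contrast as a whole is invalid. Subjects who pass a stool in the unit at both visits are unaffected by the fallback, and for the rest the dilution may be small. The open choice between one stool and all stools is a secondary matter of precision. The change is worth making because it is cheap and concerns a primary endpoint.

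**What to change.** 1. Apply the same stool rule at every visit: for example, bile acid concentration in the first stool passed after admission, with later stools as supportive data.
2. Record the date and time of passage of every stool, and relate it to the last metformin dose taken or the first one resumed.
3. Where practicable, use as fallback a stool passed shortly before admission, in the same drug state, in place of the first stool after discharge.
4. Flag stools passed after the switch at that visit's discharge, including Visit 2 when Visit 3 is dropped. Present the Visit 1 to Visit 3 faecal contrast with and without them.

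**Cost.** These are changes to procedure and analysis wording, plus home collection kits. Because nobody knows before admission whether a fallback will be needed, some home stools will be collected and not used. A pre-admission stool also precedes the standardised meal and the profiling that it is meant to accompany. The analysis without post-switch stools will have slightly fewer samples from about 12 subjects. No change to when metformin is stopped or restarted is proposed.

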### Blood Sample Collection

Blood samples for pharmacokinetic analysis of metformin will be collected at the time points indicated in Section 4.4, Time and Events Table. The actual date and time of each blood sample collection will be recorded. The timing of PK samples may be altered and/or PK samples may be obtained at additional time points to ensure thorough PK monitoring. Details of PK blood sample collection (including volume to be collected), processing, storage and shipping procedures are provided in the Study Procedures Manual (SPM).

### Bile Sample collection (EnteroTest)

[figure not shown]

The Entero-Test allows us to sample duodenal bile. It takes the form of a capsule and has dimensions of approximately 2 cm by 0.5 cm. The subject is given approximately 500ml of water and asked to swallow the capsule.

Once swallowed the string will makes its way through the digestive tract until in position at around 4 hours after ingestion. A food cue is given to encourage the release of bile onto the string. It entails showing the volunteer images of appetising foods and asking them to imaging eating them for approximately 60 seconds. This is followed by releasing orange zest scent under the nostrils and giving a food morsel. These three elements make up the cue. After completing the food cue the at a pre determined time point Entero-Test should be withdrawn by simply pulling the string out of the subject. This should take no more than 30 seconds.

At that point, the string should be visually analysed for signs of bile (yellow staining present) or should have a pH test performed if the string is not stained. The pH test is included in the Entero-Test packaging and comes with a colour indicator.

Duodenal bile samples will be collected as described in the Time and Events Table (Section 4.4) according to the following schedule:

- Entero-Test capsule swallowed approximately 6 hrs after evening meal on Day 1. Entero-Test withdrawn 8 hrs later on Day 2.
- The gall bladder will be emptied by offering a food stimulus approximately 1 hour prior to withdrawal.
- String samples will be prepared per the SPM and shipped to GSK for analysis

### Food Cue

Exposure to food cues may include:

- Images of high calorie / appetising food
- Scent of orange zest
- The sight and smell of recently cooked, highly appetising food
- Sham feeding - a subject will be given a morsel of high fat food to chew and will be asked to remove the food from their mouth prior to swallowing.
- A morsel of high fat food for the subject to ingest

These food cues may be used in combination or separately at the time points identified in Section 4.4 (Time and Events Table). The decision of which cues will be used and when are dependent on the subject and any dietary restrictions they may have.

## Safety

Planned timepoints for all safety assessments are listed in the Time and Events Table (Section 4.4). Additional time points for safety tests (such as vital signs, physical exams and laboratory safety tests) may be added during the course of the study based on newly available data to ensure appropriate safety monitoring. Samples taken during study visits will be taken following a period of overnight fasting.

Physical Exams

- A complete physical examination will include assessments of the head, eyes, ears, nose, throat, skin, thyroid, neurological, lungs, cardiovascular, abdomen (liver and spleen), lymph nodes and extremities. Height and weight will also be measured and recorded.
- A brief physical examination will include assessments of the skin, lungs, cardiovascular system, and abdomen (liver and spleen).

Vital Signs

- Vital sign measurements will include systolic and diastolic blood pressure and pulse rate.

## Pharmacokinetics

### Blood Sample Collection

Blood samples for pharmacokinetic analysis of metformin will be collected at the time points indicated in Section 4.4, Time and Events Table. The actual date and time of each blood sample collection will be recorded. The timing of PK samples may be altered and/or PK samples may be obtained at additional time points to ensure thorough PK monitoring.

Details of PK blood sample collection (including volume to be collected), processing, storage and shipping procedures are provided in the Study Procedures Manual (SPM).

### Sample Analysis

Plasma analysis will be performed under the management of Worldwide Bioanalysis, DMPK, GlaxoSmithKline. Concentrations of metformin will be determined in plasma samples using the currently approved analytical methodology. Raw data will be stored in the GLP Archives, GlaxoSmithKline.

## Biomarker(s)/Pharmacodynamic Markers

### Exploratory Biomarkers

With the subject’s consent, blood samples will be collected during this study and may be used for the purposes of measuring novel biomarkers to identify factors that may influence T2DM and related metabolic conditions such as dyslipidemia and obesity , as well as the biological and clinical responses to metformin. If relevant, this approach will be extended to include the identification of biomarkers associated with adverse events.

Samples will be collected at the timepoints indicated in Section 4.4. The timing of the collections may be adjusted on the basis of emerging PK or PD data from this study or other new information in order to ensure optimal evaluation of the PD endpoints.

- Novel candidate biomarkers and subsequently discovered biomarkers of the biological response associated with T2DM or medically related conditions and/or the action of metformin identified by application of peptide analysis of plasma samples.
- Metabolomic analysis of blood samples, initially providing a quantitative measurement of bile acids from serum samples.
- Quantitative measurement of bile acids from faeces.
- Qualitative measurement of bile acids from the Entero-Test.

Details of the biomarker sample collection (including quantity of sample to be collected), processing, storage and shipping procedures are to be provided in the Study Procedures Manual (SPM).

All samples may be retained for a maximum of 15 years after the last subject completes the trial.

# Lifestyle And/or Dietary Restrictions

## Meals and Dietary Restrictions

Subjects will be encouraged to maintain their usual diet as well as their exercise routine.

### Caffeine, Alcohol, and Tobacco

- During each dosing session, subjects will abstain from ingesting caffeine- or xanthine-containing products (e.g. coffee, tea, cola drinks, chocolate) for 24 hours prior to the start of dosing until collection of the final pharmacokinetic and or pharmacodynamic sample during each session.
- During each dosing session, subjects will abstain from alcohol for 24 hours prior to the start of dosing until collection of the final pharmacokinetic and or pharmacodynamic sample during each session.
- Subjects who use tobacco products will be instructed that use of nicotine-containing products (including nicotine patches) will not be permitted while they are in the Clinical Unit.

